## Abstract

**Rationale::**

Halitosis is an unpleasant odor that emanates from the mouth. Studies show halitosis returns in a week, after treatment with PDT. Probably, bacteria living in the periodontal sulcus could recolonize the dorsum of the tongue. Until nowadays, there are no study in adult population that associates halitosis and periodontal treatment with follow-up evaluation. The aim of this randomized, controlled, single-blinded clinical trial is to treat oral halitosis in healthy adults with photodynamic therapy (PDT), associated with periodontal treatment and follow them up for 3 months.

**Patient concerns::**

the concerns assessments will be done over the study using anamnesis interviews and specific questionnaire.

**Diagnoses::**

halitosis will be evaluated by OralChroma.

**Interventions::**

The participants (n = 40) with halitosis will be randomized into 2 groups: G1-treatment with PDT (n = 20) or G2-cleaning of the tongue with a tongue scraper (n = 20).

**Outcomes::**

Halitosis will be evaluated by measuring volatile sulfur compounds using gas chromatography. After the treatments, a second evaluation will be performed, along with a microbiological analysis (RT-PCR) for the identification of the bacteria *T. denticola*. The assessment of halitosis and the microbiological analysis will be repeated. After that, patients will receive periodontal treatment. The participants will return after 1 week and 3 months for an additional evaluation. Quality of life will be measured by *Oral Health Impact Profile questionnaire* (OHIP-14).

**Lessons::**

This protocol will determine the effectiveness of phototherapy regarding the reduction of halitosis in adults. clinicaltrials.gov NCT 03996915.

**Ethics and dissemination::**

This protocol received approval from the Human Research Ethics Committee of *Universidade Nove de Julho* (certificate number: 3.257.104). The data will be published in a peer-reviewed periodical.

## Introduction

1

Halitosis is known as an unpleasant odor from the mouth being a sign or symptom of imbalance.^[1,2]^ Its prevalence in the world is approximately 31.8%.^[3]^ The source of halitosis may be intraoral or extraoral.^[4]^ Halitosis of extraoral source originates in the upper airways or has a metabolic/systemic origin.^[2,5]^ Halitosis of intraoral source is the result of the degradation of organic substrates by anaerobic bacteria and the production of volatile sulfur compounds (VSC).^[5,6]^ Among the most important and common causes in the oral cavity are: lingual plaque (51%), periodontal disease (13%), or a combination of both (22%).^[2,3,7–9]^ The concentration of mucin in the saliva causes adhesion of the same to the lingual dorsum, especially in the region of the posterior third. In addition, desquamated epithelial cells from the buccal mucosa and proteolytic anaerobic microorganisms find 2 types of substrates: saliva proteins and proteins from desquamated epithelial cells. This set forms a whitish layer in this region of the tongue called tongue coating.^[9]^

A recent study evaluated the microbioma associated with halitosis. Among the most frequent bacteria we can mention *Treponema denticola*, *Porphyromonas gingivalis*, *Prevotella intermedia*, *Fusobacterium nucleatum* and *Campylobacter rectus*.^[10–13]^ These microorganisms release the VSCs which are products, resulting from the metabolism of these microorganisms. Among the main VSCs we can mention: hydrogen sulphide (SH_2_) - found on the back of the tongue, methylmercaptanes (CH_3_SH) - present in periodontal disease and dimethyl sulphide (CH_3_SCH_3_) of extraoral origin.^[14–17]^ The diagnosis of halitosis can be performed by gas chromatography, using an objective method, such as OralChroma (Abilit Corporation, Miyamae-KU Kawasaki-shi, Kanagawa, Japan).^[3,13,14]^

Treatment of halitosis can be done in several ways, including chemical reduction of microorganisms with mouthwashes (chlorhexidine 0.012%, essential oils and triclosan), mechanical reduction with a scraper or lingual brush and masking of the odor (chewing gum, spray and tablets).^[3]^ Recently, antimicrobial photodynamic therapy (PDT) has been studied as an alternative in the treatment of halitosis.^[18,19]^ PDT consists of the association of a photosensitizer (PS) that, by absorbing visible light at a suitable wavelength, releases reactive oxygen species.^[20]^ By absorbing energy, oxygen passes from the fundamental singlet state to the excited, short-lived singlet state. Once in this state, the PS may lose energy by nonradioactive, radioactive (fluorescence) processes or convert to the triplet state via intersystem intersection. From the triplet state (whose lifetime is longer compared to singlet), the PS can lose energy by nonradioactive, radioactive (phosphorescence) processes or participate in the formation of reactive oxygen species by electron transfer.^[21]^ This process is known as type I reaction or transfer of energy to molecular oxygen, generating singlet oxygen (type II reaction). This reaction generates energy, which is transferred to the oxygen molecules of the bacterium, leading to cell death.^[22]^

Although PDT is known as an immediate result treatment, 1 study^[8]^ shows that after 7 days, participants returned to baseline halitosis values, which underscores the statement that any treatment employed for halitosis should be accompanied with periodontal treatment. Also, the majority of halitosis studies focus in young adults, adolescents and children.^[8,23]^ There is a lack of halitosis study in older adults.

## Methods

2

A single-center, randomized, controlled, single-blind clinical trial was designed in accordance with the criteria recommended for interventional trials in the SPIRIT statement. The protocol was approved by the Research Ethics Committee of Nove de Julho University (UNINOVE), number # 3.257.104 and registered at clinicaltrials.gov NCT 03996915. The study is in accordance with the *Declaration of Helsinki*. Patients who accept to participate will sign the Informed written consent form after verbal and written explanation of the study.

All data collected and laboratory samples will be identified and maintained confidential. Only the main investigators (authors of this article) will have complete access to the set of clean data.

The sample will comprise of 40 older adults’ patients (50 years or older) with halitosis. After agreeing to participate, patients will be evaluated in different moments: baseline- before halitosis treatments (T0), immediately after halitosis treatment (T1), after periodontal treatment (T2), after 1 week (T3) and three months later (T4). The clinical assessment and the PDT treatment will be performed by the same researcher, in all 4 moments at the Dental Clinic at Nove de Julho University – UNINOVE, São Paulo, Brazil, from September 2018 until March 2019. The measurements were performed by another researcher, who does not know the nature of treatments.

### Sample size calculation

2.1

The size effect was calculated: 
[figure not shown]

If the normal distribution hypothesis is rejected, the sample size should be corrected by approximately 5%. By observing statistical samples from the reference Mota et al, 2016^[8]^; to estimate the mean values and sample variance, we obtain the following sample sizes for each group:

### Inclusion and exclusion criteria

2.2

Participants in this study will be evaluated to meet the eligibility criteria: both genders, with at least 10 teeth, PSR 0, 1 or 2, without any changes in the anatomy of the back of the tongue (geographical or fissured tongue) and positive halitosis (SH2 level higher than 112 ppb).

The following patients will be excluded: smokers or ex-smokers for less than 5 years and patients with hypersensitivity to the photosensitizer (PS).

### Calibration of examiner

2.3

An experiment examiner will perform training exercises to maximize the reproducibility of measurements. Then, 10 individuals with positive halitosis will be evaluated using the OralChroma device. These individuals will be excluded of the study. The intraclass correlation coefficient (ICC) will be calculated, and an intra-examiner agreement (≥0.90) with regard to the halitosis must be ≥0.90.

### Periodontal examination

2.4

An experienced and specialist investigator will use the *periodontal screening and recording* (PSR) system to assess the patients. PSR is a reliable, quick, and reproducible method for identifying patients, that may require a more complete evaluation of their periodontal health status. Using this system, the professional designates the patient's month in sextants and uses a probe with a 0.5 mm balled-end with a colored band extending from the 3.5 to the 5.5 mm área.^[24]^ Six sites around each tooth are probed. The code (0, 1, 2, 3, or 4) for charting is determined by how much of the colored band on a PSR probe is visible when it is inserted into the gingival sulcus: 0- colored area of probe remains completely visible in the deepest crevice in the sextante; no calculus or defective margins are detected; gingival tissues are healthy with no bleeding after gentle probing. 1- colored area of probe remains completely visible in the deepest probing depth in the sextant; no calculus or margins are detected; there is bleeding after gentle probing. 2- colored area of probe remains completely visible in the deepest probing depth in the sextante; supra- or subgingival calculus and/or defective margins are detected. 3- colored area of probe remains partly visible in the deepest probing depth in the sextant. 4- colored area of probe completely disappears, indicating probing depth of greater than 5.5 mm. Each sextant is assigned a code based on the highest probing value obtained on any tooth in that sextant.^[24,25]^ Subjects having 1 or more sextants code 3 or 4 require a complete evaluation of periodontal status, with specific treatment and will not be included in this study.

### Randomization

2.5

An external researcher who will not participate in this study will perform randomization through the Microsoft Excel program, version 2017. The same researcher will randomize into 5 blocks with 4 patients (1:1) and groups will be designated as A or B. The letters (A or B), drawn will be placed into opaque envelopes labeled with sequential numbers. The envelopes will be sealed and remain in the same numerical order in a safe place until treatments. This data will only be revealed after statistical analysis. As the study will be performed in a single-blinded manner, the operator will not know which kind of treatment will be performed. The patient will not be blinded because the nature of treatments (PDT and tongue scrapers).

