### Design

2.6

This is a controlled, randomized, single-blind clinical trial:

G1 – (experimental group -PDT) 20 patients with halitosis, 1 session of PDT will be performed with the PS. PS will be applied in enough quantity to cover the middle third and back of the tongue and wait for 5 minutes. The irradiation will be performed with low intensity laser λ = 660 nm, in 6 points, 9 J per point and radiant exposure of 318 J/cm^2^.G2 – (positive control group - tongue scrapper) 20 patients with halitosis treatment tongue scraping will be performed by the same operator. Posterior-anterior movements will be performed with the scraper over the lingual dorsum in order to promote the mechanical removal of tongue coating.

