## Discussion

3

PDT for the treatment of halitosis is known by causing immediate effects results in an unpleasant odor that emanating from the mouth.^[18]^ However, one study shows halitosis returns in a week after treatment with PDT.^[8]^

Probably, bacteria residing in the periodontal sulcus could recolonize the dorsum of the tongue, therefore we design this study promoting a complete mouth cleaning at once, in order to verify 1 week and 3-month follow-up. We think that immediate effects of PDT should be prolonged by complete one session decontamination of the mouth, by periodontal treatment.

Treatment of halitosis can be done in several ways, including chemical reduction of microorganisms with mouthwashes (chlorhexidine 0.012%, essential oils and triclosan), mechanical reduction with a tongue scraper, masking of the odor (chewing gum, spray, and tablets).^[3]^ However, these treatments may present disadvantages, such as excessive excoriation of the tongue surface with transudation and desquamation, worsening halitosis and causing discomfort when eating acid or bitter foods.^[8]^

PDT has been shown good results in treating halitosis,^[18,19]^ there are no reports of adverse effects or toxicity.^[20,22,30,31]^ As control, will be used a comparative group that will be treated with lingual scraper, the most conventional therapy in the treatment of halitosis.^[8]^

Patients with changes in the anatomy of the back of the tongue (geographical or fissured tongue) will not be included in the study. The fissures and modified papilla may favor the bacterial accumulation predisposing halitosis.^[32]^ Smokers and newly ex-smokers will be excluded, because the air exhaled by them can be mistaken for halitosis.^[33]^ Participants will be randomized in 1:1 equivalence group because both treatments are effective, and we do not expect adverse effects. Also, we decide to block the sample in 5 blocks of 4 patients, because of equivalence in the number of patients in both groups in case of we decide to include 1 more group. We expect a higher drop out because halitosis is a slight health problem and we expect some difficult to convince them to realize 2 follow up. When we achieve 8 patients per group, we will decide for a third treatment group.

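### The stated blocking scheme, 5 blocks of 4, allocates 20 patients, but the trial is planned for 40

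*Protocol article*

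**What the plan says.** The planned size is stated consistently. The abstract, under Interventions, says "The participants (n = 40) with halitosis will be randomized into 2 groups", with 20 in each. The Methods section (2) says "The sample will comprise of 40 older adults’ patients (50 years or older) with halitosis". The Design section (2.6) describes each arm with 20 patients: "G1 – (experimental group -PDT) 20 patients with halitosis, 1 session of PDT will be performed with the PS" and "G2 – (positive control group - tongue scrapper) 20 patients with halitosis treatment tongue scraping will be performed by the same operator".

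The allocation procedure is in section 2.5, Randomization: "The same researcher will randomize into 5 blocks with 4 patients (1:1) and groups will be designated as A or B". The same section has an external researcher draw the letters and place them in sealed, opaque, sequentially numbered envelopes. It does not say how many envelopes there are.

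The Discussion returns to the scheme and gives a reason for it: "we decide to block the sample in 5 blocks of 4 patients, because of equivalence in the number of patients in both groups". It links the choice to the possibility of adding another group, to be decided once 8 patients per group have been reached.

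No part of the article mentions further blocks, a second list or a later extension of the list.

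**The concern.** The number of blocks multiplied by the block size should equal the number of patients to be randomised. Here the product is half of it. This is not a detail left to a fuller document: the article states both figures, and they disagree. The same two block figures stand in the Methods and again in the Discussion, where they are applied to the sample as a whole, so no other sentence corrects them.

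At stake is the allocation of the second half of the trial. The drawn letters are what goes into the envelopes, so a list made exactly as described ends at patient 20. What happens to patients 21 to 40 is not specified: neither how their allocations are generated, nor who holds them, nor whether they are concealed in the same way.

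**Working it through.** **Inputs**
- Planned total: 40 (abstract, Interventions; Methods, section 2).
- Planned per group: 20 and 20 (abstract, Interventions; Design, section 2.6).
- Blocks: 5, with 4 patients each, at 1:1 (Randomization, section 2.5; Discussion).

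**Step 1. The plan's own total.** 20 + 20 = 40. The planned size is internally consistent.

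**Step 2. Allocations from the stated scheme.** Allocations = number of blocks × block size = 5 × 4 = 20. At 1:1 this is 20 / 2 = 10 per group. The shortfall is 40 − 20 = 20 patients, or 20 / 40 = 50% of the sample. The scheme does not reproduce 40.

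**Step 3. What would reproduce 40.**

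| Kept fixed | Solved for | Result |
|---|---|---|
| Block size 4 | Number of blocks = 40 / 4 | 10 blocks of 4 |
| 5 blocks | Block size = 40 / 5 | 5 blocks of 8 (4 per arm) |

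Both give 20 per group. The arithmetic alone does not show which was intended.

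**Step 4. Does the possible third group explain the gap?** Eight patients in each of two groups is 16 patients, which is 16 / 4 = 4 blocks of 4. The decision point therefore comes before the 20 stated allocations run out, but the article does not say that the list is to be produced in stages. Nor does a block of 4 divide equally among three groups (4 / 3 = 1.33), and a third arm of the same size would call for more allocations, not fewer.

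**Step 5. Illustration of halving the sample.** The effect size and the resulting group sizes in section 2.1 are in content that is not shown, so this trial's power at 10 per group cannot be computed. As an assumption, take a range of power at 20 per group. For each value, solve for the standardised difference d in a two-sample t test at two-sided 5%, then evaluate the same d at 10 per group.

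| Assumed power at 20 per group | Implied d | Power at 10 per group |
|---|---|---|
| 70% | 0.806 | 0.400 |
| 80% | 0.909 | 0.486 |
| 90% | 1.052 | 0.605 |
| 95% | 1.170 | 0.697 |

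These figures matter only if recruitment really ended when the stated list ran out.

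**The case against.** The strongest reply is that the mismatch is one of wording and would do no harm in practice. Three parts of that reply deserve weight.

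First, the phrase in section 2.5 may mean four patients per arm in each block, and 5 × 8 = 40 fits exactly. That is a real possibility, and it is why one cannot say that 10 blocks of 4 is the only repair. But neither passage says per arm, and the Discussion's wording reads naturally as total block size. If blocks of 8 were meant, the text still needs correcting.

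Second, the external researcher could simply draw more blocks in the same way and seal them in numbered envelopes, with concealment intact. This also stands. A reader might infer that half the patients have no envelope, that the trial will stop at 10 per group, or that concealment is lost for patients 21 to 40. The document supports none of these: the number of envelopes is never given, no passage plans a stop at 20, and the total of 40 is stated repeatedly. What the document does show is narrower: the described scheme ends at 20 and nothing describes what follows.

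Third, repeating the figures in the Discussion does not prove intent, since a phrase can be carried over from one section to another. That is fair, but it also means that nothing in the text resolves the conflict.

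A reader might also extend the point to the fixed block size, because an operator who knows earlier allocations can sometimes predict the last ones in a block. With blocks of 4, the fourth is always determined and the third in 2 of the 6 possible sequences, so (1 + 1/3) / 4 = 33% of allocations are predictable. With blocks of 8 the share is 20%. These are upper bounds, for someone who knows the block size and every earlier allocation. Fixed blocks with external generation and sealed, numbered opaque envelopes are common practice. This is a separate design preference and not part of the error.

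**Conclusion.** The contradiction stands. The allocation scheme as written yields 20 allocations, 10 per group, against a planned 40, 20 per group. It therefore covers 50% of the sample, and either the number of blocks or the block size is misstated. The conclusion rests on reading a block of 4 patients as the total block size; on the only other reading that reaches 40, the text is still wrong as worded.

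The consequence is an unspecified allocation for patients 21 to 40, not a demonstrated loss of power or of concealment. The range of about 40% to 70% power at 10 per group is an illustration that depends on an assumed 70% to 95% at 20 per group and on the trial actually stopping at 20. It should be corrected because it concerns the operative randomisation instruction, even though the correction is small.

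**What to change.** In section 2.5 and in the Discussion, restate the scheme so that the number of blocks times the block size equals 40: either 10 blocks of 4, or 5 blocks of 8 with four per arm in each. The authors must say which was meant. Add to section 2.5 that the external researcher generates all 40 allocations and seals 40 sequentially numbered opaque envelopes before the first patient is enrolled. If some allocations have already been drawn, state how many, and how the remainder were or will be generated and concealed.

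The cost is one sentence in two places and, if the existing list is short, a list of 40. No extra patients or staff are needed. Varying the block size is optional.

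### The stated randomisation blocks (5 blocks of 4) give 20 allocations, but the trial randomises 40 patients, so the scheme as written covers only half the sample

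*Protocol article*

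**What the plan says.** Section 2.5 (Randomization) describes allocation by an external researcher using a spreadsheet: "The same researcher will randomize into 5 blocks with 4 patients (1:1) and groups will be designated as A or B". The drawn letters go into sealed, opaque, sequentially numbered envelopes. The number of envelopes is not given.

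The Discussion (section 3) repeats the scheme and gives a reason for it: "we decide to block the sample in 5 blocks of 4 patients, because of equivalence in the number of patients in both groups". It adds that a third group may be considered once each group has 8 patients, and that a fairly high dropout is expected.

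The sample size appears in three places, and they agree:
- Abstract, Interventions: "The participants (n = 40) with halitosis will be randomized into 2 groups".
- Methods (section 2): "The sample will comprise of 40 older adults’ patients (50 years or older) with halitosis".
- Design (section 2.6): "G1 – (experimental group -PDT) 20 patients with halitosis" and "G2 – (positive control group - tongue scrapper) 20 patients with halitosis".

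**The concern.** The number of blocks, the block size, the ratio and the sample size are all stated, and they cannot all be true. This is not a detail that an article leaves to a fuller protocol or an analysis plan. The article gives the figures, and they conflict.

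The block scheme is an operative instruction, because the envelopes are filled from it. Someone who follows section 2.5 literally reaches the end of the list after patient 20 and finds no rule for patients 21 to 40. A reader of the eventual report also cannot tell which block size was used. That matters in an unblinded comparison with fixed blocks. Whoever delivers the treatment sees what was given, and the shorter the block, the more easily its remaining assignments can be worked out.

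**Working it through.** **Inputs, all from the protocol article**
- Blocks: 5 (sections 2.5 and 3).
- Block size: 4 patients (sections 2.5 and 3).
- Ratio: 1:1 (sections 2.5 and 3).
- Planned sample: 40 (Abstract, section 2), 20 in G1 and 20 in G2 (section 2.6).

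**Step 1. Check the sample figures against each other.** G1 + G2 = 20 + 20 = 40. This reproduces the stated total.

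**Step 2. Count the allocations in the stated scheme.** Blocks × block size = 5 × 4 = 20. At 1:1 that is 20 / 2 = 10 per group. Neither the total of 40 nor the group size of 20 is reproduced.

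**Step 3. Size of the gap.** 40 − 20 = 20 patients without an allocation under the stated scheme, and 20 / 40 = 50%.

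**Step 4. What would give 40.**
- Keeping blocks of 4: 40 / 4 = 10 blocks, each with 2 A and 2 B, giving 20 per group.
- Keeping 5 blocks: 40 / 5 = 8 patients per block, each with 4 A and 4 B, giving 20 per group.

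**Step 5. Does anything else in the article close the gap?**
- *Dropout.* Allowing for it only raises the number to be randomised. With n = 20 / (1 − dropout), rounded up, an assumed dropout of 10%, 20% or 30% gives 23, 25 or 29 per group. These rates are assumptions; the article states none.
- *Third group.* The decision point of 8 per group uses 2 × 8 = 16 allocations, which leaves 20 − 16 = 4 on the list as stated. A third group would need more allocations, and a block of 4 cannot be divided equally among three groups.
- *Reading the 4 as 4 per group.* This gives 5 × (4 + 4) = 40 and is the only reading of the stated 5 and 4 that works. Neither section 2.5 nor the Discussion says it.
- *Further blocks or a second list.* None is described.

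The sample size calculation in section 2.1 is in a figure that is not shown. The check does not need it, because the planned 40 is stated elsewhere.

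**The case against.** The strongest reply is that this is a slip in wording and not a fault in the randomisation itself. If the 4 is read as 4 per group in each block, five blocks give exactly the stated 20 per group. The Discussion also counts recruitment per group, and 8 per group would then be two complete blocks. The repetition in the Discussion may show only that a phrase was reused, not that a list of 20 was drawn up. Much of this stands: a reporting error is the likely explanation. It does not settle the matter, because 8 per group is equally four complete blocks of 4, and neither place says that the 4 is per group.

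Two stronger readings are tempting, and the article does not support either.
- A reader might infer that half the sample would be allocated without concealment. The article does not state how many envelopes there are, does not call the list final, and nowhere says that any patient is allocated openly. If the external researcher prepared and sealed further blocks in the same way, concealment would be kept. Making blocks later is not in itself a source of selection bias.
- A reader might infer that the trial would stop at 10 per group and lose power and precision. Every statement of the sample size says 40, and no passage suggests stopping at 20. Any power figure for that case would be hypothetical and would also need an effect size that the visible text does not give.

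**Conclusion.** The block scheme is wrong as written. It yields 20 allocations, 10 per group, against a planned 40, 20 per group, so it provides no allocation for 20 of the 40 patients (50%). This rests only on figures in the article and on reading its block size literally as the number of patients in a block.

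The likely cause is a misreported scheme, either 10 blocks of 4 or 5 blocks of 8, and the text does not allow a choice between them. The documents do not show lost concealment, selection bias or reduced power, and the point does not depend on any of these. It still needs correcting, because the wrong figure sits in the rule from which the envelopes are made.

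**What to change.** In sections 2.5 and 3, restate the number of blocks and the block size so that their product covers all 40 patients. Either of these would do:
- 10 blocks of 4, each with 2 A and 2 B; or
- 5 blocks of 8, each with 4 A and 4 B, if 4 per group was what was meant.

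Add that the external researcher generates the full list before the first patient is enrolled, and that the sealed envelopes are numbered 1 to 40. If allocation has already begun, report the scheme actually used.

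The cost is one corrected sentence in each of two places and, if only 20 envelopes were prepared, 40 − 20 = 20 more. No patients, visits or analyses change.
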